**Figure 1 F1:**
[figure not shown]
Design at baseline

#### Sequential Behaviour Tailoring (SeqBT) condition

After receiving the health risk appraisal, individuals in the SeqBT condition are invited to choose one of the health behaviours for which they have received a red or orange traffic light. Respondents are encouraged to change the behaviour for which they are motivated most. After receiving additional questions regarding the various psychosocial constructs of the selected lifestyle behaviour, they receive personal advice on this behaviour which aims at helping to change this health behaviour during the first year of the study.

At the follow-up measurements, individuals in this condition are asked to fill out a questionnaire about all behaviours. Again, they receive the health risk appraisal, including an overview consisting of five traffic lights. In cases where a respondent has successfully changed the selected behaviour, the option to choose a second behaviour in the second year is provided. They are free to select one of the behaviours for which they receive a red or orange traffic light. In cases where respondents have not changed the first behaviour, they will be invited to change the behaviour for which they are motivated most in the second year. This may be the same behaviour as chosen in the first year, but the respondents may also select another lifestyle behaviour for which they have obtained a red or orange traffic light. Afterwards, they receive the questionnaire containing items about perceptions (beliefs) regarding the behaviour they have selected to focus on as well as personal advice.

If respondents fill in the test in the meantime, which means that they re-visit the programme without having received an invitation for a follow-up measurement, they only have to answer the questions concerning the selected behaviour in order to receive ipsative feedback on their chosen topic and personal advice if they are interested.

#### Simultaneous Behaviour Tailoring (SimBT) condition

Upon receiving the health risk appraisal, participants of the SimBT condition are not explicitly asked to select one behaviour which is in contrast to the SeqBT condition. In cases where these participants do not adhere to the recommendation of one or more of the lifestyle behaviours, they obtain additional questions (psychosocial constructs) as well as personal advice on all behaviours for which they receive a red or orange traffic light in the health risk appraisal.

At every follow-up visit/re-visit, individuals are asked to fill out questions about all five lifestyle behaviours. In this way, the programme can check on which behaviours the individual should receive personal advice concerning his or her perceptions. Moreover, they receive ipsative feedback concerning all five behaviours.

#### Control condition

During the first visit of the programme, respondents in the control condition receive the health risk appraisal. Afterwards, this group only receives e-mails requesting them to fill out questionnaires about the five lifestyle behaviours at follow-up at 12 months (T1) and 24 months (T2). The control group does not receive any personal advice throughout the term of this study.

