### Participants, inclusion criteria and procedure

The study is part of an initiative of different Dutch Regional Health Authorities (RHAs) of the provinces North-Brabant and Zeeland. Our CT programme is partly integrated in the *Adult Health Monitor 2009 *which is conducted by the RHAs. With this monitoring instrument, the health status of people living in the Netherlands is assessed. Every four years, a representative sample of the population aged between 18 and 65 years is recruited in order to fill out this questionnaire. It contains the following topics: demographics; aspects of general health (e.g., physical health, mental health, social health, lifestyle behaviours); and health related topics (e.g., social and physical environment) [47]. As part of an additional service, participants completing this monitor online subsequently obtain the opportunity to receive tailored feedback about their health behaviour via the new CT programme. Therefore, some data the person fills out during the *Adult Health Monitor *(e.g., demographics and data regarding the five lifestyle behaviours: smoking, alcohol intake, fruit consumption, vegetable consumption and physical activity) are copied to the CT programme. Before this, participants receive information about the purpose of the current study and an explanation of the use/handling of their data. We ask for written informed consent for their participation in the project. Confidentiality is ensured and it is explained to respondents that they could withdraw participation at any moment.

Approximately three weeks after completing the monitor, participants who are interested in obtaining tailored feedback about their health behaviour receive an e-mail including an invitation to log in to the CT programme by use of their personal login code and password. After successfully logging in, respondents receive the health risk appraisal (i.e., feedback concerning their lifestyle and information about whether they meet the public health guidelines) based on their answers to the *Adult Health Monitor*, and the experimental groups receive some additional questions (i.e., attitude, social influence, preparatory action plans, self-efficacy, coping plans) and personal advice. The different parts of the programme will be described in detail below.

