### The two experimental groups and the control group

As presented in Figure 1, the three groups differ in the amount of feedback they receive. The experimental groups have the option to obtain health risk appraisals and personal advice as often as they want whereas the control condition only receives the health risk appraisal once. Every time the experimental groups visit the programme, *ipsative feedback *is given about their health behaviour. This implies that the health behaviour scores of the current visit are compared to the scores of the last visit; feedback is given about a potential change. Furthermore, all scores are saved and illustrated in a graph in order to give the respondent the option to monitor the total change process at a glance. Ipsative feedback is not available for the control group.

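### Answering at 12 and 24 months earns feedback in both experimental arms but not in the control arm: a foreseeable, partly avoidable risk of differential non-response, of unknown size and direction

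*Protocol article*

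**What the plan says.** All places are in the Methods of the protocol article.

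- **Who takes part** (*Participants, inclusion criteria and procedure*): the invitation to log in goes to those wanting feedback: "participants who are interested in obtaining tailored feedback about their health behaviour receive an e-mail".
- **Control arm** (*Control condition*; *The two experimental groups and the control group*): one appraisal at the first visit, since "the control condition only receives the health risk appraisal once". Then: "Afterwards, this group only receives e-mails requesting them to fill out questionnaires about the five lifestyle behaviours at follow-up", at 12 and 24 months. Also "Ipsative feedback is not available for the control group" and "The control group does not receive any personal advice throughout the term of this study".
- **Sequential arm**, at the follow-up measurements: "Again, they receive the health risk appraisal, including an overview consisting of five traffic lights". After the participant selects a behaviour: "Afterwards, they receive the questionnaire containing items about perceptions (beliefs) regarding the behaviour they have selected to focus on as well as personal advice".
- **Simultaneous arm**, at every follow-up or re-visit: questions on all five behaviours, which decide where advice is given. "Moreover, they receive ipsative feedback concerning all five behaviours".
- **Retention** (*Attrition prevention*): 300 prizes of 50 Euros for completers, with no restriction by arm; three-monthly prompts to half of the experimental participants; monthly website updates.
- **Dropout** (*Power analysis*): one overall allowance, leading to about 3,285 participants, with nothing by arm or by outcome.

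**The concern.** Participants were invited because they wanted feedback on their own behaviour. At T1 and T2 two arms get it for answering and the third does not. Those two measurements supply the outcomes for the first objective, so the motive to respond differs by arm just where response matters most.

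The listed retention measures do not close the gap. The prize draw is common to all arms, the prompts go only to experimental participants, and the website updates are not aimed at controls. An overall dropout allowance protects the number of responders, not the comparability of the arms.

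If the link between outcome and response also differs by arm, both experimental-control contrasts are biased. Analysis cannot reliably repair non-response that depends on the unobserved follow-up outcome. The comparison of the two experimental arms with each other is outside this point.

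**Working it through.** **1. The plan's own figure.** 3 × 219 = 657 smokers; 657 / 0.25 = 2,628; 2,628 / 0.80 = 3,285. The 20% loss is an assumption, as the article states no rate. It prints 2,826 as the intermediate total, which its own inputs do not give; that is a separate matter and nothing below rests on it. What counts here is that the allowance is a single overall one.

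**2. Formula.** Let p be the true proportion improved in an arm, a the response among the improved and b the response among the unimproved. Then:

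- overall response = p·a + (1 − p)·b
- rate seen among responders = p·a / [p·a + (1 − p)·b]

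If a = b, the observed rate equals p. Response of 75% in one arm and 85% in another, unrelated to outcome, therefore gives zero bias among responders. Only if non-responders were counted as failures would it matter: (0.85 − 0.75) × p, or 1 to 2 points for p of 10% to 20%.

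**3. Outcome-related response in controls only.** Assumed: p = 0.15, a = 0.80, b = 0.70 or 0.60, and experimental response unrelated to outcome.

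- b = 0.70: 0.120 / (0.120 + 0.595) = 16.8%; overall response 71.5%
- b = 0.60: 0.120 / (0.120 + 0.510) = 19.0%; overall response 63.0%

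The control rate is inflated by 1.8 to 4.0 points. With a true experimental rate of 25%, the 10-point difference would be seen as 25 − 16.8 = 8.2 down to 25 − 19.0 = 6.0 points: bias toward no effect.

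**4. The same pattern in both arms.** Assumed true improvement 15% in controls and 25% in the experimental arm.

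- b = 0.70: experimental 0.200 / (0.200 + 0.525) = 27.6%; difference 27.6 − 16.8 = 10.8 points
- b = 0.60: experimental 0.200 / (0.200 + 0.450) = 30.8%; difference, before rounding the two rates, 11.7 points

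The bias is +0.8 to +1.7 points, in the opposite direction to step 3.

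**5. No true effect, other assumed patterns** (true rate 10% to 20% in both arms).

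| Control response (improved / unimproved) | Experimental response (improved / unimproved) | Bias in the difference |
|---|---|---|
| 80% / 80% | 90% / 70% | +2.5 to +4.3 points |
| 90% / 60% | 90% / 85% | −3.8 to −6.3 points |
| 90% / 70% | 90% / 70% | 0 |

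The sign depends on which arm has the stronger link between outcome and response. The documents do not settle that.

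**The case against.** A reader might infer that the design makes outcome-related dropout certain, or that it costs 18-40% of the 10-point target difference (1.8/10 to 4.0/10). The documents support neither. Different incentives imply at most different response rates, and these alone leave a comparison of responders unbiased. No section shows that controls answer when they have good news. The 18-40% also requires experimental response to be unrelated to outcome. That is doubtful, because experimental participants who have not improved face red or orange lights and a comparison with their last visit, and may stay away too. Step 4 shows the effect of allowing for that.

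Three further objections stand in part:

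- Controls do get something: the baseline appraisal is personal feedback, and the prize draw is open to them. A common incentive may support their response, but it does not remove the difference in feedback.
- Repeat appraisal, feedback on change and the renewed choice of behaviour at T1 are the intervention under test. Giving them to controls at T1 would change the comparator. This stands in full, and limits any remedy to T2.
- Reminders and missing-data methods may be set out in documents not shown, and nothing is counted as missing on that score. This does not alter the asymmetry itself, which the article fixes.

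**Conclusion.** The asymmetry is explicit, and nothing described in the article offsets it. It creates a foreseeable risk of differential, possibly outcome-related, non-response in both experimental-control contrasts. It does not establish a bias.

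Size and direction are unknown. Under the stated assumptions the range runs from zero, through +0.8 to +1.7 points with the same pattern in both arms, to 1.8 to 4.0 points toward no effect with the pattern in controls only; other patterns give either sign. All response and improvement rates used are assumptions; only the 10-point target is the article's. Against that target the larger values would matter.

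The T1 part is inherent in the comparison and should stay. The T2 part can be reduced cheaply, so this is a worthwhile low-cost improvement rather than a fault that invalidates the design.

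**What to change.** In the controls' T2 invitation, and nowhere earlier, state that on submitting the 24-month questionnaire they immediately receive the health risk appraisal on their new answers and access to the existing personal advice modules. Amend *The two experimental groups and the control group* and *Control condition* to say that further feedback is withheld from controls until T2 is submitted.

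Because the offer is announced only at T2 and released after the last answers are in, it cannot change behaviour during the 24 months or create a waiting-list effect. The comparator up to T2 is unchanged.

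Cost: one sentence in one e-mail and a switch in the automated programme, with no extra staff. Downsides: the site must stay open to controls after T2, and T1 response is not helped. The gain at T2 cannot be estimated from the documents. Making the return more alike does not guarantee zero bias either (step 4), but it removes an avoidable reason for response to differ by arm.

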### Primary and secondary outcomes

Our first objective is to compare the effectiveness of the two different strategies for changing lifestyle with each other as well as with a control group.

In addition to the effect studies, we will also gather and analyse data to realize additional outcomes:

#### Process evaluation

Process evaluations will be executed to assess levels of personalization and appreciation and to analyse which elements of the CT programme were most attractive and successful. We aim at gathering process evaluation data to analyse the factors facilitating and hindering the use of the web-based modules. All participants receive questions concerning the *website *(5 items; e.g., "In my opinion, the website is user-friendly"; totally agree - totally disagree), the *health risk appraisal *(12 items; e.g., "The health risk appraisal gives a good overview of my lifestyle"; totally agree - totally disagree) and two *general questions *(i.e., "Do you intend to re-visit the website in the future?"; yes, definitely - no, definitely not; "Do you have any general comments concerning the programme?"; open question). The two experimental groups additionally receive questions regarding the personal advice (15 items; e.g., "The pieces of advice are informative"; totally agree - totally disagree). We will compare the evaluations of the three different groups to analyse differences with regard to the process evaluation data.

#### Subgroup differences

We aim at exploring potential differences between high SES and low SES groups, different age groups, men and women, and healthy and unhealthy people (defined by the items about health status).

### Power analysis

The power analysis is based on detecting 10% differences in behaviour between the different conditions. Power analysis calculations differ per behaviour. Estimations for finding effects on the lifestyle behaviours of smoking and alcohol consumption were the most conservative power analyses resulting in the greatest number of respondents needed. Since approximately 25% to 30% of the population smoke and almost similar percentages are estimated for non-compliance with the alcohol guideline [7], sample size calculations are highly determined by these two groups. In order to be able to find a significant difference of 10% in quit rates and improved behaviour between the conditions, power calculations (alpha=.80; p=.05) indicate that 219 smoking persons per cell are needed, resulting in a total of 657 smokers. Hence, if approximately 25% of the adult population smokes this requires a total study sample of 2,826 persons. A similar conclusion can be drawn for the persons not adhering to the Dutch alcohol recommendations. Correcting for dropout this indicates that the total sample size for this study will be approximately 3,285 persons. The sample will be sufficient to assess changes in the other behaviours (fruit and vegetable consumption and physical activity).

### Attrition prevention

Different strategies are used in order to prevent attrition and to encourage participation in the long run. First, participants are eligible to win prizes. Participants completing the study stand a chance to win one of 300 prizes of 50 Euros. Second, half of the respondents of the experimental groups receive e-mail prompts, including invitations to visit the tailoring programme, every three months, in order to be able to analyse whether pro-active prompting will enhance visiting the website and using computer tailored feedback more intensively. Third, new information is placed on the website monthly in order to keep it up to date and make it attractive for people to re-visit the website.

### Statistical analyses

General descriptive statistics will be used to describe the characteristics of the participants and the main findings concerning the public health guidelines. With regard to the assessment of behavioural effects and differences between the three groups, logistic as well as linear regression analyses will be performed using Statistical Package for the Social Sciences (SPSS) version 15. With regard to the process evaluation, descriptive statistics will be used, such as frequencies, means, standard deviations and ranges. Satisfaction with the programme and ideas for improvement will also be analysed by summarizing the answers to the open-ended question and comparing different attitudes and suggestions. In order to explore potential differences between groups (e.g., low SES versus high SES, age groups, gender), regression techniques and latent cluster analyses will be used.

## Discussion

The results of this study are of importance for the future development and implementation of CT programmes, which aim at stimulating healthy lifestyles in order to prevent chronic diseases. Positively changing a set of health risk behaviours, i.e., smoking, high alcohol consumption, bad nutrition and physical inactivity, is becoming increasingly common since these changes are relevant for the primary prevention of cardiovascular related diseases and cancer [1,2]. Due to the target of several behaviours and health problems, by using a tailored web-based programme, these kinds of programmes are considered to be potentially cost-effective [11].

Internet-based health education programmes have become popular in recent years. To our knowledge, however, few were tested in a RCT to analyse effects on multiple behaviours. Addressing smoking, alcohol consumption, fruit and vegetable intake, and physical activity at the same time, is one fundamental part of recent developments. In addition, we compare a simultaneous behaviour tailoring approach with a sequential behaviour tailoring approach. Hence, we will experimentally test which tailoring lifestyle approach is more effective and appreciated. This study will thus yield results about the need for differential lifestyle approaches. An optimal use of (one of) the different strategies could increase the effectiveness of web-based CT lifestyle programmes. Research is also important in order to assess whether the effectiveness and appreciation of the programme differs between various subgroups.

Furthermore, a unique element of this project is that our CT programme is offered as an additional service of the RHAs in the Dutch regions of North-Brabant and Zeeland within the regular health monitoring they provide to adults. The integration of the CT programme to the *Adult Health Monitor 2009 *brings along various advantages. First, the RHAs may extend and improve their health education task by offering tailored feedback regarding lifestyle behaviours to their respondents. Second, the personal advice may be an extra stimulus for people to participate in the *Adult Health Monitor*. Third, the *Adult Health Monitor *of the two provinces has a total reach of nearly 100,000 inhabitants. Due to the integration of our CT programme into the 'Adult Health Monitor', a large number of people within the Dutch population may be reached.
